### Data collection tools

The intrapartum data collection tool has been adapted from an existing document that was used as an audit tool during the introduction of SWI at Site One. For self reported postnatal data, the data collection tool previously published and used in the Australian study by Peart et al. [16] has been made available for use. This tool has been tested for face readability, language and face validity. The instrument will be administered by a researcher blinded to the particular technique used.

### Statistical analysis

Demographic and other baseline characteristics will be analysed for comparability between groups to assess the adequacy of randomisation. Differences in VAS pain score between the two groups will be analysed using Student's t-test and analysis of variance (non-parametric tests used if data is highly clustered toward extremes). Data analysis for the primary outcome will determine if the treatment effect lies within the a priori defined non-inferiority margin (± 1 cm) and the null effect (0 cm) at a one-sided alpha of 0.025. The pre-specified non-inferiority margin was based on a one cm (95% CI 0.6-1.4 cm) minimally clinically significant difference reported for VAS in severe pain [14]. The Mann-Whitney U test will be utilised for non-parametric data and chi-squared test for categorical variables. Women who give birth or elect for narcotic and/or regional analgesia after the collection of the primary measure (VAS score 30 minutes post injection) but before the completion of the secondary outcomes (VAS up to 120 mins) will be included in the trial. Women giving birth or electing for narcotic and/or regional anaesthesia prior to the collection of the primary outcome measure will be included in the Intention to Treat (ITT) analysis. The conservative nature of ITT may obscure differences between treatments groups therefore increasing the chance of falsely declaring equivalence [19]. To address this, some authors have recommended that Per Protocol (PP) analysis also be conducted alongside ITT to provide a more robust conclusion if both methods support the non-inferiority [9,20]. Other authors [21] argue that the benefits of ITT analysis continue to outweigh the PP approach. As it is unlikely that participants in this trial will cross from one intervention to another, the ITT approach will be used unless the dropout out rate exceeds the estimated margin allowed of 20%. Should the dropout rate exceed 20% then a PP analysis will also be conducted. Figure 4 outlines possible scenarios for the outcome of the data analysis based on the pre-defined noninferiority margin, indicated as the shaded area. Error bars indicate 90% confidence intervals (CI). If the CI is completely to the left of zero, the treatment is inferior (scenario A). Scenarios C,D and E indicate noninferiority as the CI lies within the specified margin (shaded area). Scenario F would indicate superiority. An inconclusive result (scenario B) is unlikely as the sample size is sufficiently powered to provide a result [22].

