## Abstract

**Background:**

Almost one third of women suffer continuous lower back pain during labour. Evidence from three systematic reviews demonstrates that sterile water injections (SWI) provide statistically and clinically significant pain relief in women experiencing continuous lower back pain during labour. The most effective technique to administer SWI is yet to be determined. Therefore, the aim of this study is to determine if the single injection SWI technique is no less effective than the routinely used four injection SWI method in reducing continuous lower back pain during labour.

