**Statistical analysis:**

Sample size was calculated to achieve 90% power at an alpha of 0.025 to detect a non-inferiority margin of ≤ 1 cm on the VAS, using a one-sided, two-sample t-test. Baseline demographic and clinical characteristics will be analysed for comparability between groups. Differences in primary (VAS pain score) and secondary outcomes between groups will be analysed by intention to treat and per protocol analysis using Student's t-test and ANOVA.

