Systematic reviews [3,5] and meta-analysis [6] have reported a significant reduction in self-reported pain measures in groups receiving SWI compared with controls. Authors concluded that SWI are an effective therapeutic intervention for the management of continuous back pain during labour. However, the included randomised controlled trials (RCT) were heterogeneous and incorporated different SWI techniques (single and four-injection SWI methods), methods of administration (intradermal or subcutaneous), and comparison groups (normal saline, transcutaneous electronic nerve stimulation and "standard care" defined as massage, counter pressure and water immersion). Authors of the systematic reviews [3,5] highlight that the analgesic efficacy obtained following administration of a single SWI at the most painful point [7] appear comparable to that obtained using the four injection SWI technique. The analgesic benefit of the single SWI method is further supported by results of a more recent randomised controlled trial (RCT) [8] which compared a single SWI to a placebo. The comparable analgesic benefit observed for both techniques has led authors to conclude there is need for further research [3,5]. There have been no trials conducted to date comparing the two SWI techniques.

There may be important clinical benefits in demonstrating the comparable analgesic efficacy of a single versus four needle SWI technique. The relative reduction in discomfort associated with the single injection procedure may increase the woman's satisfaction and acceptability with SWI treatment during labour, and willingness to use the procedure again in the future. In addition, improved resource allocation can be expected as only one midwife is required to administer a single SWI compared with the current recommendation for two midwives to administer the four injection technique. Therefore, the aim of this study is to compare a single intradermal SWI technique with the standard four injection intradermal technique in the degree and duration of analgesic benefit.

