#### Primary outcome

Decrease in pain measured by VAS at 30 minutes post-intervention.

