#### Secondary outcomes

Secondary outcomes will include:

a) Pain score measured by VAS 10, 60, 90 and 120 mins post-intervention

b) Level of administration discomfort associated with SWI procedure (measured by VAS at 10 minutes post SWI)

c) Subsequent analgesia use (pharmacological and non-pharmacological)

d) Mode of birth

e) Likelihood to use again with subsequent labour

f) Patient satisfaction with analgesic effect

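### Duration of relief is part of the aim, but the 1 cm margin is applied only at 30 minutes, and a difference test at 60 to 120 minutes cannot show that one injection lasts as long as four

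*Protocol article*

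**What the plan says.** All references are to the protocol article.

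- **Aim.** The Background ends with the aim to "compare a single intradermal SWI technique with the standard four injection intradermal technique in the degree and duration of analgesic benefit". The abstract words the aim without duration: to "determine if the single injection SWI technique is no less effective than the routinely used four injection SWI method".
- **Outcomes.** The primary outcome is "Decrease in pain measured by VAS at 30 minutes post-intervention". The first secondary outcome is "Pain score measured by VAS 10, 60, 90 and 120 mins post-intervention".
- **Analysis of VAS scores.** The Statistical analysis section says "Differences in VAS pain score between the two groups will be analysed using Student's t-test and analysis of variance". The abstract says "Differences in primary (VAS pain score) and secondary outcomes between groups will be analysed by intention to treat and per protocol analysis", and names the t-test and ANOVA as the methods.
- **Margin.** The Statistical analysis section limits it to one outcome: "Data analysis for the primary outcome will determine if the treatment effect lies within the a priori defined non-inferiority margin". No criterion is given for the later scores.
- **Events between 30 and 120 minutes.** Women who give birth or choose narcotic or regional analgesia in this window stay in the trial. The text after Figure 4 adds that any repeat injection uses the four injection technique, in either arm, and that scores around the repeat are reported separately. It does not say what then happens to the woman's scheduled 60 to 120 minute scores.

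**The concern.** Whether relief lasts can be judged only from the 60, 90 and 120 minute scores. For those times the article names difference analyses and no margin. The Methods/design and Hypothesis sections explain that showing one treatment to be no worse than another needs a margin, but that reasoning is not carried beyond 30 minutes.

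A single injection that wears off sooner could therefore be reported as not significantly different at the later times, beside a headline that it is no less effective. The fewer women with usable scores at 120 minutes, the more likely that outcome becomes. A difference test drifts towards the reassuring answer as data are lost, whereas a margin-based reading drifts towards an inconclusive one.

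**Working it through.** **Inputs.** From the Sample size section: margin 1 cm, SD 2.5 cm, one-sided alpha 0.025, true difference 0, 133 per arm, power 90%. Assumed here: a two-sided 0.05 level for the later difference tests (none is stated for secondary outcomes), the same SD at the later times, and 80, 66 or 50 evaluable women per arm as illustrations of loss by 120 minutes.

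**Step 1: the plan's own figure.** With n per arm, the standard error is SE = 2.5 × √(2/n), and power comes from the noncentral t with 2n − 2 degrees of freedom and noncentrality 1/SE.

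- n = 132: power 0.8993.
- n = 133: SE = 2.5 × √(2/133) = 0.3066, noncentrality 1/0.3066 = 3.26, power 0.9015.

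So 133 per arm reproduces. It is the size for the 30 minute test.

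**Step 2: difference test when one injection is truly 1 cm worse.** The chance of a non-significant result is the probability that |t| stays below the two-sided 0.05 critical value, with noncentrality 1/SE. The last column is the power to show non-inferiority when the true difference is zero, at one-sided 0.025.

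| Evaluable per arm | SE (cm) | 1/SE | P(non-significant), true deficit 1 cm | Non-inferiority power, true difference 0 |
|---|---|---|---|---|
| 133 (protocol) | 0.307 | 3.26 | 0.099 | 0.901 |
| 80 (assumed) | 0.395 | 2.53 | 0.290 | 0.710 |
| 66 (assumed) | 0.435 | 2.30 | 0.374 | 0.626 |
| 50 (assumed) | 0.500 | 2.00 | 0.492 | 0.508 |

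The last two columns add to 1 because both tests use the same noncentrality and critical value.

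**Step 3: the margin-based reading.** Suppose the true deficit is exactly 1 cm and non-inferiority is declared only when the two-sided 95% confidence interval excludes a deficit of 1 cm. The wrong conclusion then has probability 0.025 at every size in the table. At 133 per arm the interval is about ±0.60 cm (1.96 × 0.3066), narrow enough to be read against 1 cm.

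**Step 4: limit of step 3.** The 0.025 holds only if the later scores reflect the allocated technique. A low score after birth or after narcotic or regional analgesia does not. Nor does a score from a single-injection woman who has since received four injections. If such events are more common in the single-injection arm, they pull the arms together and the margin test can pass too often. The article gives no event rates, so the size of this bias cannot be calculated.

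**The case against.** The strongest reply is that duration is not part of the confirmatory question. It appears as an aim once, at the end of the Background. The abstract aim, the conclusion and the Discussion speak only of being no less effective or non-inferior, the later scores are labelled secondary, and the power calculation serves the 30 minute outcome. Naming a t-test also does not by itself mean a difference-only reading, because the Sample size section calls the non-inferiority test a two-sample t-test. And at 133 per arm, the 0.10 is the ordinary type II error of a design with 90% power.

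Much of this stands and limits the weight of the point. It does not remove it: the Background aim names duration, the margin sentence is confined to the primary outcome, and the text offers nothing else by which to judge the later scores.

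Three stronger readings are tempting, and the documents do not support them.

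- **That the trial cannot conclude anything about duration.** The hypotheses state 1 cm on the VAS without naming a time, and the same estimates can be read as confidence intervals against it. The weakness lies in the analysis as written.
- **That the plan intends to read non-significance as similarity.** No sentence says so. The plan leaves the reading open.
- **That missing testing order, multiplicity control or an exploratory label is a fault.** For outcomes already called secondary, these are commonly settled in a statistical analysis plan, which is not at hand. The 10 minute score concerns onset more than duration and is no part of this point.

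**Conclusion.** The point holds in a limited form. Followed as written, the analysis could not support a statement that relief from one injection lasts as long as relief from four. If the true deficit at a later time were 1 cm, a difference test would fail to show it with probability 0.10 at 133 per arm, and 0.29 to 0.49 at 80 to 50 per arm.

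These figures rest on the protocol's SD of 2.5 cm holding at later times and on an assumed two-sided 0.05 level. The sizes below 133 are illustrations, since the article gives no expected number of evaluable women after 30 minutes. Reading intervals against the margin repairs the inference. It does not by itself guarantee a 2.5% error rate, because births, other analgesia and repeat injections can make the arms look alike. The 30 minute primary analysis is not affected by this point.

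**What to change.** In the Statistical analysis section:

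1. For 60, 90 and 120 minutes, report the between-arm difference in VAS change with a two-sided 95% confidence interval, read against the same 1 cm margin, as supportive secondary results.
2. State that a non-significant difference will not be read as similar effect.
3. Add a sensitivity analysis in which scores recorded after birth, after narcotic or regional analgesia, or after a repeat injection are not counted as relief from the allocated technique. Fix in advance how those scores are treated. This concerns only the analysis of the scores, not the care given.

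The change takes a few sentences. It needs no new VAS measurements, though the sensitivity analysis depends on the times of birth, other analgesia and repeat injection being available. The downside is that the later times may often be inconclusive. With zero true difference, the power to show non-inferiority at one time is 0.71 at 80 per arm and 0.51 at 50, so duration may have to be reported as not shown.

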**Methods/design:**

The trial protocol was developed in consultation with an interdisciplinary team of clinical researchers. We aim to recruit 319 women presenting at term, seeking analgesia for continuous severe lower back pain during labour. Participants will be recruited from two major maternity hospitals in Australia. Randomised participants are allocated to receive a four or single intradermal needle SWI technique. The primary outcome is the change in self-reported pain measured by visual analogue scale at baseline and thirty minutes post intervention. Secondary outcomes include VAS change scores at 10, 60, 90 and 120 min, analgesia use, mode of birth and maternal satisfaction.

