### Inclusion criteria

Participants eligible for the study will be defined as:

Women at term (between 37 and 42 weeks)

Nulliparous or multiparous

Singleton pregnancy

Cephalic presentation

First stage labour (spontaneous or induced)

No previous analgesia pharmacological analgesia (nitrous oxide inhalation, narcotics)

Back pain assessed by VAS as ≥7

Ability to give informed consent. This may exclude women of non-English speaking backgrounds, where an interpreter is unavailable, and those women whose consent is required to be provided by a parent or guardian.

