### Sample size

A sample size of 133 in each group will be required to achieve 90% power to detect non-inferiority using a one-sided, two-sample t-test. The significance (alpha) of the test is 0.025. The non-inferiority margin is ≤ 1 cm on the VAS and the true difference between the means is assumed to be zero (cms). A standard deviation (SD) of ± 2.5 on the VAS was conservatively estimated from results reported in a recent meta-analysis [6] of SWI studies. As consent and randomisation will occur in the birth suite, attrition is expected to be minimal. However, we have estimated a 20% attrition to account for cases of precipitate birth prior to the assessment of the primary outcome, or other unforseen reasons for withdrawal such as emergency caesarean section. Thus a total of 319 participants will be required.

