### Randomisation

The randomisation schedule for Site One will be prepared by a statistician using a computer-generated list of random numbers. Blinding of allocation to the study intervention will be undertaken using opaque sealed envelopes prepared by Site One administrative staff. A separate randomisation sequence was generated for Site Two in permuted blocks of four to ensure an equal number of participants across both arms of the trial where smaller recruitment numbers are expected. Blinded allocation at this site will be undertaken using similarly prepared opaque sealed envelopes (Figure 3).

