### Data collection

Upon randomisation the attending Midwife will document the following data:

• UR number

• Gravity and Parity

• Gestation

• Spontaneous or induced labour

• Findings of last vaginal exam and time

• VAS score and time

• Time of administration

Following administration of SWI the following data will be recorded:

• VAS related to analgesia effect at 10 mins

• VAS related to discomfort felt during the procedure (at 10 mins)

• VAS related to analgesic effect at 30 minute intervals up to 2 hours post procedure

At Site One the following data will be extracted from the obstetric database by the research midwife following birth:

• Age

• Booking weight & BMI

• Mode of birth

• Time of birth

• Any other analgesia used (pharmacological and non pharmacological)

• Model of care

• Educational level

The obstetric databases at Site One and Site Two vary slightly in the data items collected. As separate data collection forms have been generated for the randomisation process for Site Two, the data collection forms have been amended to account for any differences in information captured by the database.

The following self-reported data will be sought from the woman within 48 hours following birth:

• Perceived satisfaction with SWI administration

• Perceived satisfaction with SWI analgesic benefit

• Likelihood to use again with subsequent labour

• Likelihood to recommend to SWI to others

Data will be collected by the Midwife caring for the labouring woman then returned to a securely locked cupboard. Completed data forms will be de-identified and entered into a password protected electronic database. Identified data collection forms will be kept in locked storage for 15 years. Data collection forms at the second site will be stored in a locked cupboard and collected on a fortnightly basis. Data will be entered into a Microsoft Excel spreadsheet and transmitted as a password protected file

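### Free improvement, not an error: the primary t-test on VAS change could be replaced by a linear model on arm, baseline VAS and site, which is valid, needs no new data and may be somewhat more precise

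*Protocol article*

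**What the plan says.** The Abstract (Methods/design) describes the primary outcome as "the change in self-reported pain measured by visual analogue scale at baseline and thirty minutes post intervention". The Primary outcome section words it as "Decrease in pain measured by VAS at 30 minutes post-intervention".

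Statistical analysis names the method: "Differences in VAS pain score between the two groups will be analysed using Student's t-test and analysis of variance". The factors of the analysis of variance are not listed. The Sample size section works out the number needed "to detect non-inferiority using a one-sided, two-sample t-test", which is unadjusted by definition.

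Two variables that could enter the analysis are already available:

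- **Baseline VAS.** Data collection lists "VAS score and time" among the items recorded at randomisation. The Inclusion criteria limit its range: "Back pain assessed by VAS as ≥7".
- **Site.** Under Randomisation, Site One has its own computer-generated list with no blocking stated. For the other site, "A separate randomisation sequence was generated for Site Two in permuted blocks of four".

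Nowhere does the article name baseline VAS or site as a covariate, factor or stratum of the primary comparison.

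**The concern.** A change score treats each centimetre of baseline pain as worth exactly one centimetre at 30 minutes. When every woman enters between 7 and 10 on a 10 cm scale, that slope need not be near 1. If it is not, subtracting baseline leaves variation that regression on baseline would remove. Site is a stratum of the randomisation by construction, and usual practice is to carry such strata into the model.

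What is at stake is precision. The conclusion depends on whether a confidence limit clears 1 cm, so a wider interval than necessary raises the chance of an inconclusive result. Naming the covariates in advance also settles what happens if the planned baseline comparison shows an imbalance.

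**Working it through.** **Inputs from the Protocol article (Sample size).** Margin 1 cm, true difference 0, SD 2.5, one-sided alpha 0.025, power 90%, 133 per arm.

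**Assumed, not in the document.** The 2.5 is the SD of change (the article does not say whether it refers to change or to the 30-minute score). Baseline SD s0 is 0.8 to 1.0. Correlation r between baseline and 30-minute VAS is 0 to 0.5. The limits on s0 follow from the entry range: a uniform spread over 7 to 10 has SD 3/√12 = 0.87, and a single-peaked distribution on an interval of length 3 cannot exceed SD 3/3 = 1.0.

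**Step 1: the plan's own figure.** n per arm = 2 × (1.960 + 1.282)² × 2.5² / 1² = 131.3, so 132 by the normal approximation. With the noncentral t, power is 89.9% at 132 and 90.1% at 133. The stated 133 is reproduced.

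**Step 2: residual variance after regression on baseline.** Let s1 be the SD of the 30-minute score.

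- From s0² + s1² − 2·r·s0·s1 = 6.25, s1 = r·s0 + √(6.25 − s0²(1 − r²)).
- The slope is b = r·s1/s0.
- The residual variance is s1²(1 − r²), which equals 6.25 − (1 − b)²·s0².

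The saving is (1 − b)²·s0². It is never negative, and it is zero when b = 1. Power uses 133 per arm and 262 degrees of freedom (264 for the t-test, less two).

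| s0 | r | slope b | residual variance | ratio to 6.25 | power |
|---|---|---|---|---|---|
| 0.8 | 0 | 0 | 5.61 | 0.90 | 92.9% |
| 0.8 | 0.1 | 0.31 | 5.94 | 0.95 | 91.5% |
| 0.8 | 0.3 | 0.98 | 6.25 | 1.00 | 90.1% |
| 0.8 | 0.5 | 1.75 | 5.89 | 0.94 | 91.8% |
| 1.0 | 0 | 0 | 5.25 | 0.84 | 94.4% |
| 1.0 | 0.1 | 0.24 | 5.67 | 0.91 | 92.7% |
| 1.0 | 0.3 | 0.78 | 6.20 | 0.99 | 90.4% |
| 1.0 | 0.5 | 1.42 | 6.07 | 0.97 | 91.0% |

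In interval terms, the 95% half-width is 1.96 × 2.5 × √(2/133) = 0.60 cm for the change score. At best (variance 5.25) it is 0.55 cm.

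**Step 3: sensitivity to the meaning of 2.5.** If it is the SD of the 30-minute score, the same ranges of s0 and r give an SD of change of 2.18 to 2.69. Power at 133 per arm is then 85.5% to 96.1% for the t-test on change and 90.1% to 96.3% for regression on baseline.

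**Step 4: site.** The article gives no between-site variance. If site explained 1%, 5% or 10% of the variance (assumed), power at 133 per arm with a site term would be 90.4%, 91.5% or 92.9%. If the arms were perfectly balanced within site, the unadjusted test's one-sided type I error would be 0.0244, 0.0222 or 0.0194, all on the conservative side of 0.025.

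**The case against.** The strongest reply is that nothing here is wrong. Design and analysis agree: the trial is powered for a two-sample t-test and plans one, and the stated power reproduces. That stands, and it is why the point is offered as an improvement only.

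A second reply is that model terms are often left to an analysis plan, and that an analysis of variance with unlisted factors might include site. This stands in part, since for that half of the sentence the absence of site is read from silence. The t-test, however, is named in the Abstract, in Sample size and in Statistical analysis, so the article does fix an unadjusted comparison.

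Three stronger readings are tempting, and the document does not support them:

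- *The plan ignores baseline.* It does not; baseline enters every woman's change score. Only the slope is fixed.
- *Chance imbalance in baseline passes straight into the result.* A change score carries only (b − 1) times the imbalance. With s0 of 0.8 to 1.0 and 133 per arm, the 95% range of that imbalance is ±1.96 × s0 × √(2/133), or ±0.19 to ±0.24 cm. The t-test's interval already allows for it.
- *The gain is large.* A variance ratio of 0.77 and power of 96% would need a baseline SD of 1.2 with zero correlation. On a 7 to 10 range, an SD of 1.2 requires women clustered at both ends.

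On site, only the smaller Site Two is stated to be blocked, which limits any mismatch between randomisation and analysis.

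**Conclusion.** The point holds as a modest gain in efficiency and pre-specification. The unadjusted comparison is unbiased, its type I error is held or slightly conservative, and it meets the planned 90% power at 133 per arm if 2.5 is the SD of change.

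With baseline SD 0.8 to 1.0 and correlation 0 to 0.5, regression on baseline leaves 84% to 100% of the change-score variance and gives about 90% to 94% power. The upper end needs zero correlation. Near a slope of 1 (r about 0.3 to 0.4 here) there is no gain. The benefit from site cannot be sized from the document. A reader should not infer that the primary analysis is invalid or the trial underpowered because of this choice.

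**What to change.** In Statistical analysis, name as the primary analysis a linear model of 30-minute VAS on arm, baseline VAS and site. Judge the adjusted mean difference against the 1 cm margin at the stated one-sided alpha of 0.025. Keep the unadjusted t-test on change as a supporting analysis.

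Using change as the response gives the same treatment estimate once baseline is in the model. This also makes it immaterial that the article calls the primary measure a decrease in one section and the 30-minute score in another.

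The cost is a sentence of analysis wording and two degrees of freedom (264 to 262 at 133 per arm). No new data are needed, and the sample size need not change.

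### The primary variable is worded as change from baseline in the outcome definitions but as a VAS pain score in the analysis text, and nothing says which is tested against the 1 cm margin

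*Protocol article*

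**What the plan says.** Two places define the primary outcome, and both make it a change. The abstract (Methods/design) says: "The primary outcome is the change in self-reported pain measured by visual analogue scale at baseline and thirty minutes post intervention". The Primary outcome section says: "Decrease in pain measured by VAS at 30 minutes post-intervention".

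The analysis text uses another term. The abstract (Statistical analysis) has "Differences in primary (VAS pain score) and secondary outcomes between groups". The Statistical analysis section says "Differences in VAS pain score between the two groups will be analysed using Student's t-test and analysis of variance", and later refers to "the collection of the primary measure (VAS score 30 minutes post injection".

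The secondary VAS outcomes show the same split: "VAS change scores at 10, 60, 90 and 120 min" in the abstract, but "Pain score measured by VAS 10, 60, 90 and 120 mins post-intervention" under Secondary outcomes.

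The Hypothesis section states a difference between techniques of at least 1 cm (null) or less than 1 cm (alternative) on the VAS, without saying whether this is a difference in scores or in changes. The Sample size section takes an SD of 2.5 from a meta-analysis and does not tie it to either variable. A baseline VAS is recorded (Data collection), but no baseline adjustment is stated.

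**The concern.** The decrease and the 30-minute score give two different unadjusted estimates, with different standard errors, to set against the same 1 cm margin. If both terms remain in the document, either could be reported as the primary result, and the choice could be made after the data are seen. The verdict depends on where one confidence limit falls, so a small shift between the two estimates matters when the result is near the margin. The planned power also depends on which variable the SD of 2.5 describes.

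**Working it through.** **1. The plan's own figure.** Inputs from Sample size: margin 1 cm, SD 2.5, true difference 0, one-sided alpha 0.025, power 90%. The normal approximation gives n = 2 × 2.5² × (1.960 + 1.282)² / 1² = 131.4, so 132 per group. With the exact noncentral t, power is 89.9% at 132 and 90.1% at 133. The stated 133 per group reproduces, for whichever variable has an SD of 2.5.

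**2. How the two estimates relate.** Let B be the baseline VAS and Y the 30-minute VAS, with each difference taken as single minus four.
- Deficit of the single injection on the score: D_Y.
- Deficit on the decrease (B − Y): D_Y − D_B.

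The gap between them is exactly D_B, the baseline difference between arms. Randomisation gives it an expected value of zero, so both estimate the same true difference.

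**3. Size of the gap.** The documents give neither the baseline SD nor the baseline/30-minute correlation r, so both are assumptions. Entry at VAS ≥ 7 confines baseline to 7–10, so its SD is small; I take 1.0, with a range of 0.8 to 1.2. At 133 per group the SE of D_B is 1.0 × √(2/133) = 0.123 cm, a 95% range of ±0.24 cm (±0.19 to ±0.29 cm over the range).

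**4. SD and power for the change, if 2.5 is the SD of the score.** SD of change = √(2.5² + 1.0² − 2 × r × 2.5 × 1.0).

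| r | SD of change | Power at 133 per group |
|---|---|---|
| 0 | 2.69 | 85.5% |
| 0.2 | 2.50 | 90.1% |
| 0.3 | 2.40 | 92.3% |
| 0.5 | 2.18 | 96.1% |

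Power for the score is 90.1% throughout. If instead 2.5 is the SD of the change, the score SD runs from 2.29 (r = 0) to 2.85 (r = 0.5), and power for the score from 94.4% to 81.5%.

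**5. How often the verdicts differ.** Non-inferiority is declared when the estimated deficit + 1.969 × SD × √(2/133) is below 1 cm. For the score this means an estimated deficit below 1 − 1.969 × 2.5 × 0.1226 = 0.396 cm. Treating the two estimates as bivariate normal, with score SD 2.5, baseline SD 1.0 and r from 0 to 0.5:
- True difference 0 (the protocol's assumption): verdicts differ in about 5% to 7% of trials.
- True deficit 0.5 cm: about 12% to 15%.
- True deficit 1 cm (the margin): each test alone declares non-inferiority in about 2.5% of trials, and at least one of the two does so in about 3.4%.

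Widening the baseline SD to 0.8–1.2 gives about 4% to 9% at a true difference of zero, and about 10% to 19% at 0.4 cm.

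**6. Baseline adjustment.** Regress either variable on group and B. Since the decrease is B − Y, its group coefficient is minus that for Y, with the same standard error. ANCOVA therefore gives one treatment estimate, apart from sign, and the ambiguity disappears.

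**The case against.** The strongest reply is that the two places that define the outcome agree on change, and that the Statistical analysis section tests the primary outcome against the margin, which points back to that definition. On this view the analysis wording is shorthand for all the VAS outcomes, and a full analysis plan may fix the variable. This has weight, and it is why the fix adopts the change. It does not remove the point: the t-test sentence and the abstract's parenthesis name the variable compared, and the secondary outcomes really are listed both ways. That is a conflict within the article, not detail left to another document.

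A reader might infer more than the text supports:

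- **That the 30-minute score has been made the endpoint.** The words "the collection of the primary measure (VAS score 30 minutes post injection" stand in a sentence about women who give birth or take other analgesia after that reading. They can simply mark a time point, since a change also needs that reading.
- **That the data form records a third quantity.** "VAS related to analgesic effect at 30 minute intervals up to 2 hours post procedure" might suggest a relief scale. The form also rates discomfort from the procedure at 10 minutes, so the label plausibly separates back pain from injection pain. No relief scale is mentioned anywhere.
- **That the hypothesis has the wrong sign.** The Hypothesis section gives no order of subtraction, and it labels the null as inferiority, so the intended direction is clear.
- **That the SD of 2.5 must be wrong for one variable.** It is described as a conservative estimate and could cover both. At r = 0.2 and baseline SD 1.0 the two SDs coincide.
- **That the type I error is inflated as planned.** Either test alone keeps its nominal level. The 3.4% arises only if the favourable result is chosen afterwards, which the protocol does not propose.

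**Conclusion.** The point holds as an inconsistency in the primary variable that should be resolved. The outcome definitions say change, the analysis wording says pain score, and nothing shown settles which is tested against the margin. The consequence is moderate. There is no bias, because both analyses target the same mean difference, and the gap between them is a chance baseline difference of roughly ±0.2 to 0.3 cm. It matters mainly for results near the margin. The sizes rest on assumed values for the baseline SD and the correlation, and on the score SD being 2.5; the documents confirm none of these.

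**What to change.** - In the abstract (Statistical analysis), Hypothesis and Statistical analysis, name one variable, the one already defined as primary: the decrease in back pain VAS from baseline to 30 minutes. Define the 10, 60, 90 and 120 minute outcomes in the same way.
- State the difference as single minus four in mean decrease, with non-inferiority if the lower confidence limit, at the one-sided 0.025 level, is above -1 cm. This agrees with the existing description of Figure 4, where inferiority lies to the left of zero. Four minus single would reverse it.
- Say whether the meta-analysis SD of 2.5 is for the change or for the 30-minute score. If it is for the score, restate the power for the change (about 85% to 96% under the assumptions above).
- Consider ANCOVA on the baseline VAS, which gives the same treatment estimate for either variable. If adopted, it should replace the unadjusted test as the primary analysis and not stand beside it as a further option.

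The cost is wording, plus one check of the meta-analysis. The baseline VAS is already collected, so no further data are needed. The variable should be fixed before outcome data are examined by arm.
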